### Quality control

An independent data and safety monitoring board (DSMB) will evaluate the progress of the trial and will examine safety parameters at regular intervals (every 45 patients or every 6 months). In particular, all recurrences will be assessed to analyse whether there is a diagnostic delay caused by the study protocol. Also, all involved physicians will repetitively be asked by the primary researchers to report any potential adverse events caused by following the study protocol. These adverse events will be listed and discussed with the DSMB. The input of the study participants along with a progress report of the project leader (JW) will be supplied to the DSMB before they have a meeting. All deceased patients will be evaluated by the safety committee for cause of death and possible trial-related serious adverse effects. The DSMB committee can ask for a full report in order to discuss a specific adverse event. The DSMB will consist of an epidemiologist/statistician who is the chairman, an independent surgeon, and an independent GP. None of these members has a conflict of interest with the sponsor of the study. The advice of the DSMB will be sent to the sponsor of the study. Should the project leader decide not to fully implement the advice of the DSMB, the sponsor will send the advice to the reviewing ethics committee, including a note to substantiate why (part of) the advice of the DSMB will not be followed.

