## Methods/Design

This is a multi-centre 2 × 2 factorial randomised controlled trial. Two randomisation procedures (at the same moment) will be undertaken: one to create two groups for surgeon-led—usual care (i.e., control group)—versus GP-led follow-up and aftercare and a second randomisation for allocation of the eHealth application Oncokompas^2.0^. This factorial design results in four groups on a 1:1:1:1 ratio (Fig. 1):Usual follow-up visits and aftercare provided in secondary care (surgeon-led);Usual follow-up visits and aftercare provided in secondary care (surgeon-led) with additional use of the eHealth application Oncokompas^2.0^;Follow-up and aftercare in primary care (GP-led);Follow-up and aftercare in primary care (GP-led) with additional use of the eHealth application Oncokompas^2.0^.

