**Fig. 1 Fig1:**
[figure not shown]
Study flow chart. *GP* General practitioner

Randomisation will be performed centrally at the Academic Medical Centre in Amsterdam by using block randomisation to balance patient characteristics within each group on the basis of two variables: age and tumour stage. If a second patient of an already-participating GP is included, this patient (and all subsequent patients) will be allocated to the same follow-up/aftercare arm (i.e., primary or secondary care). The chance that two patients of the same GP will be diagnosed with colon cancer in the study period, will be eligible for inclusion in the study, and give informed consent is small. Nevertheless, we avoid having two patients of the same GP receive different care (primary care-led versus secondary care-led follow-up) as this will result in contamination. Owing to the nature of the intervention, it is not possible to conceal the allocation group from either participants or clinicians. However, the primary researchers are not involved in subsequent follow-up/aftercare appointments in any way. Recruited patients will not be informed about other patients recruited in the same trial. Similarly, no information regarding trial progress will be revealed to the participating GPs or surgeons.

The study will be conducted in eight hospitals. The number of segmental colonic resections for cancer in the participating centres ranges between 60 and 160 patients per centre annually.

If a patient (or GP) declines randomisation, the patient is asked to participate in a patients’ preference group (Fig. 1). In this arm, baseline data similar to those of the randomised study arms are gathered, but the allocation is based on the patients’ treating surgeon and patient preference.

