Costs will be discounted at 4 % and effects at 1.5 % as recommended by the Dutch guidelines for costing studies [29]. Missing cost and effect data will be imputed by using multiple imputation according to the MICE (Multiple Imputation by Chained Equations) algorithm developed by Van Buuren et al. [37]. Costs typically have a highly skewed distribution [38]. Therefore, bias-corrected and accelerated bootstrapping with 5000 replications will be used to estimate 95 % confidence intervals around the mean difference in total societal costs between the groups. Incremental cost-effectiveness ratios (ICERs) will be calculated by dividing the difference in mean total costs between the groups by the difference in mean effects between the groups. Bootstrapping will be used to estimate the uncertainty surrounding the ICERs which will be graphically presented on cost-effectiveness planes. Cost-effectiveness acceptability curves will also be estimated. Cost-effectiveness acceptability curves show the probability that care by GPs is cost-effective in comparison with usual care for a range of different ceiling ratios, thereby showing decision uncertainty [39]. The iMTA MCQ and SF-HLQ questionnaires will be sent to the participant simultaneously with the quality-of-life questionnaires (EQ-5D-5 L) to facilitate patient’s response. Besides the information provided by the patients themselves by means of the methods mentioned above, the researchers will systematically gather data directly from hospital and GP files. This information will be used to compare health-care usage and be correlated to compare health-care costs. The following items will be checked at the time intervals mentioned above: outpatient clinic visits, GP practice visits, telephone consultations, hospital admittances (number of days), laboratory tests, all medical imaging, endoscopies, referrals to (other) medical specialist care, referrals to paramedical care, and drug prescriptions. Note that health-care use in both primary and secondary care will be evaluated for patients allocated to any group of randomisation to create a complete survey of health-care use.

Each single item will be stored in the case record file created for each participant. Via this information from health-care use, the costs used by each participant will be determined by using standardised reference lists.

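### For events other than deaths and recurrences, the DSMB's physician-reported adverse event list is filtered by unblinded attribution, so its counts are not a fair comparison of GP-led with surgeon-led care

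*Protocol article*

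**What the plan says.** The Quality control section describes several routes by which safety information reaches the DSMB, which looks at safety every 45 patients or every 6 months.

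- **Physician reports.** The text says that "all involved physicians will repetitively be asked by the primary researchers" to "report any potential adverse events caused by following the study protocol". It continues: "These adverse events will be listed and discussed with the DSMB".
- **Recurrences.** Here "all recurrences will be assessed to analyse whether there is a diagnostic delay caused by the study protocol".
- **Deaths.** "All deceased patients will be evaluated by the safety committee for cause of death and possible trial-related serious adverse effects".
- **Other input.** Before each meeting the DSMB receives input from participants and a progress report from the project leader. It may also ask for a full report on a particular event.

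Methods/Design describes the first randomisation as "one to create two groups for surgeon-led—usual care (i.e., control group)—versus GP-led follow-up and aftercare". A second randomisation allocates Oncokompas2.0, so one of the two surgeon-led arms also contains a study intervention. On blinding, the randomisation paragraph says that "it is not possible to conceal the allocation group from either participants or clinicians".

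Under Economic evaluation analysis, the researchers extract health-care use from hospital and GP files for patients in every randomised group. The items include "hospital admittances (number of days".

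**The concern.** Safety monitoring usually collects serious events whatever their presumed cause and judges relatedness afterwards, so that each arm supplies a background rate for the other. Here the causal judgement is part of the request itself. It is made at the moment of reporting, by clinicians who know the allocation.

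The judgement is unlikely to work the same way on both sides. In the surgeon-led arm without Oncokompas2.0 the study asks for little beyond usual care, so a surgeon has little reason to put an event down to the protocol. Under GP-led care the setting itself is new. An event can more readily be blamed on it, but the reporting GP may also be reluctant to blame care that he or she delivered.

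At stake is the DSMB's view of the non-fatal harms, other than recurrence, that a change of setting could cause: missed complications, unplanned admissions, or late re-referral with no recurrence found. On a filtered list a real excess under GP-led care could be hidden, or an excess could appear where none exists.

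**Working it through.** **Step 1: what must be true for an event to be taken in.**

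| Route to the DSMB | Condition at entry | Who applies it |
|---|---|---|
| Recurrences | none; all are assessed | not applicable |
| Deaths | none; all are evaluated | not applicable |
| Participant input | none stated; not described as a count of events | not applicable |
| Physician-reported adverse events | potential event caused by following the protocol | unblinded physicians |

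For deaths and recurrences, causation is assessed after intake. For physician-reported events it is a condition of intake. The article nowhere asks physicians for adverse events irrespective of cause.

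**Step 2: inputs.** The Sample size section gives 75 patients per group and 300 in total (4 × 75 = 300). Each care setting combines two groups: 2 × 75 = 150. The article states no adverse event rate and no attribution rate. All risks and attribution fractions below are assumptions, chosen only to show how the filter behaves.

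**Step 3: formula.** With n patients per setting, true risk p and attributed fraction a, the expected number listed is L = n × p × a. With equal n,

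L(GP) / L(surgeon) = [p(GP) / p(surgeon)] × [a(GP) / a(surgeon)].

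The list shows the true risk ratio multiplied by the attribution ratio. It is fair only if the attribution ratio is 1.

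**Step 4: results (GP-led v surgeon-led, n = 150 each).**

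| True risk | True events | Attribution | Listed events |
|---|---|---|---|
| 10% v 10% | 15 v 15 | 50% v 50% | 7.5 v 7.5 |
| 10% v 10% | 15 v 15 | 50% v 10% | 7.5 v 1.5 |
| 10% v 10% | 15 v 15 | 50% v 0% | 7.5 v 0 |
| 5% v 5% | 7.5 v 7.5 | 50% v 10% | 3.75 v 0.75 |
| 20% v 20% | 30 v 30 | 50% v 10% | 15 v 3 |
| 25% v 15% | 37.5 v 22.5 | 30% v 50% | 11.25 v 11.25 |

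- **Row 1.** Equal attribution thins the list but does not bias the comparison.
- **Rows 2, 4 and 5.** With equal true risk, attribution of 50% v 10% gives a listed ratio of 5, whatever the risk.
- **Row 6.** A true ratio of 25/15 = 1.67 is cancelled by an attribution ratio of 30/50 = 0.6, since 1.67 × 0.6 = 1. A real excess disappears from the list.

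The filter can therefore distort in either direction. Nothing in the article fixes the attribution ratio, so neither the size nor the sign of the distortion can be calculated.

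**The case against.** The case against has six parts.

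1. **Other routes exist.** The harm most specific to GP-led follow-up, late detection of recurrence, has its own unfiltered review, and so do deaths. Participant input does not pass through physician attribution, and the recurrence review is introduced as one instance of a wider look at safety parameters. This stands and limits the point to one list and one class of events. It does not remove the point, because no systematic, unfiltered count of other serious events is described. The DSMB can ask for a full report only on an event it has heard of.
2. **The threshold is low.** The request covers any potential event, so suspicion is enough. This stands in part: the filter is softened but is still causal.
3. **Usual-care reports are possible.** A reader might infer that the list must be almost empty in the surgeon-led arms. The article does not support that. One of those arms uses Oncokompas2.0, physicians in all arms are asked, and the follow-up guideline is similar in both settings. Sparse reporting is a reasonable expectation for the arm with usual care alone, and no more.
4. **GPs are not the only reporters.** Patients under GP-led care can be referred back to hospital at any time, and hospital physicians who see them may report too. This stands. Self-judgement by the GP is one influence on attribution, not the whole of it.
5. **The figures are assumed.** This is correct. A surgeon-led attribution of 0% would build the conclusion into the input, and equal attribution gives no distortion. The table shows a mechanism, not an estimate.
6. **This is a condensed article.** The full protocol may contain general rules for serious events. That limits confidence, but the point rests on a reporting rule that the article states, not on one it omits.

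**Conclusion.** The point holds in a limited form. For events other than deaths and recurrences, the list built from physician reports is selected by unblinded attribution at entry. Attribution is likely to differ between GP-led and usual surgeon-led care, most clearly against the surgeon-led arm without Oncokompas2.0. Counts on that list should not be read as a comparison of the two settings.

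The size and direction of the distortion are unknown. The illustrations run from none (equal attribution) to a fivefold false difference (50% v 10%) and to complete masking of a 25% v 15% excess (30% v 50%), all on assumed rates. Two stronger inferences are not supported: that other harms can reach the DSMB only through this list, and that the DSMB's safety review as a whole is compromised.

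The quality-of-life analysis and the sample size are not affected. Admissions are collected in every arm in any case, so a comparison by setting will be possible at final analysis. What is missing from the stated arrangements is that comparison while the trial is running. This is a worthwhile improvement, not a critical fault.

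**What to change.** 1. In the Quality control section, remove the attribution condition for serious events. Physicians in all four arms would report them whatever the presumed cause, and relatedness would be judged afterwards, preferably by assessors who do not know the allocation. Non-serious events can stay under the present wording.
2. For each DSMB meeting, tabulate hospital admissions by care setting for all randomised patients in all four arms. Use the hospital and GP file extraction already planned for the economic evaluation, with the data available at that date, and mark each admission as planned or unplanned.
3. Leave the reviews of recurrences and deaths as they are.

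**Cost.** One extracted item has to be available earlier. Files come from eight hospitals and many GP practices at fixed follow-up times, so this is more than producing a table, and the data at any meeting will be incomplete. The planned item records admissions and days, so the planned or unplanned marker is an addition. The listing will contain some admissions unrelated to the trial. Allocation, endpoints and sample size do not change.

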### Analysis

#### Sample size

The sample size calculation is based on the primary endpoint: quality of life. In accordance with previous studies, we consider an effect of 10 units of improvement of the EORTC QLQ C30 to be clinically relevant [34]. To detect an intervention effect of 10 units of change (standard deviation of 20) in quality of life, we will need 64 participants in each group (alpha of 0.05 and power of 80 %). As we expect some drop-out, we aim for 75 patients in each group. The total sample size is therefore 300 patients. Given the sample size calculation and the factorial design of the study, the assumptions are made that the effects of the two interventions are independent and that there are no important interactions (synergy).

#### Analysis of main study parameters

All analysis will be performed according to the intention-to-treat principle. Crude data are presented with statistical comparison made between randomisation groups on the basis of chi-squared tests for binary or categorical data, the *t* test or analysis of variance as appropriate for comparing group means, and the Kruskal-Wallis test for comparing medians. For continuous normally distributed data, the analysis-of-variance test will be used. The primary analysis will be the comparison between factors, and the comparison between study arms will be part of a secondary, exploratory analysis. For these purposes, univariate and multiple linear or logistic regression analyses will be performed. Quality of life will be assessed through multi-level modelling. A two-sided *P* value of less than 0.05 will be considered statistically significant. Nevertheless, in all appropriate cases, 95 % confidence intervals will be given. Changes in health status and valuation over time will be measured by using the questionnaires mentioned above. Next to validated questionnaires and prospective monitoring of the trial endpoints, extractions from the GPs’ EMR and patients’ hospital records will be used to complete the data.

#### Economic evaluation analysis

The aims of the economic evaluation are to describe the societal costs of patients who after an operation for colon cancer receive follow-up at the hospital or by the GP and to relate these costs to the clinical effects in these groups. The time horizon of the economic evaluation is up to 5 years after surgery. A societal perspective is chosen, meaning that not only health-care costs but also patient and lost productivity costs are taken into account. Health-care utilization will be measured by using the iMTA MCQ at baseline and after 3, 6, 12, 24, 36, 48, and 60 months of follow-up [33]. Health-care costs include costs of GP care, costs of psychiatric and psychological care, costs of ambulatory and inpatient hospital care, costs of visits to allied health-care professionals such as physical therapists and social workers, costs of medication and examinations, and costs of home care. The SF-HLQ will be used to measure absenteeism from paid and unpaid work at all follow-up moments. For the valuation of health-care utilization, standard prices published in the Dutch costs guidelines will be used [35]. Medication use will be valued by using prices of the Royal Dutch Society for Pharmacy [36]. Quality of life will be measured by using the 5-level version of the EuroQol (EQ-5D-5 L) [27]. Health states will be converted to utility scores by using the Dutch tariff for the EQ-5D-5 L. Quality-adjusted life-years will be calculated by using linear interpolation between time points.

Costs will be discounted at 4 % and effects at 1.5 % as recommended by the Dutch guidelines for costing studies [29]. Missing cost and effect data will be imputed by using multiple imputation according to the MICE (Multiple Imputation by Chained Equations) algorithm developed by Van Buuren et al. [37]. Costs typically have a highly skewed distribution [38]. Therefore, bias-corrected and accelerated bootstrapping with 5000 replications will be used to estimate 95 % confidence intervals around the mean difference in total societal costs between the groups. Incremental cost-effectiveness ratios (ICERs) will be calculated by dividing the difference in mean total costs between the groups by the difference in mean effects between the groups. Bootstrapping will be used to estimate the uncertainty surrounding the ICERs which will be graphically presented on cost-effectiveness planes. Cost-effectiveness acceptability curves will also be estimated. Cost-effectiveness acceptability curves show the probability that care by GPs is cost-effective in comparison with usual care for a range of different ceiling ratios, thereby showing decision uncertainty [39]. The iMTA MCQ and SF-HLQ questionnaires will be sent to the participant simultaneously with the quality-of-life questionnaires (EQ-5D-5 L) to facilitate patient’s response. Besides the information provided by the patients themselves by means of the methods mentioned above, the researchers will systematically gather data directly from hospital and GP files. This information will be used to compare health-care usage and be correlated to compare health-care costs. The following items will be checked at the time intervals mentioned above: outpatient clinic visits, GP practice visits, telephone consultations, hospital admittances (number of days), laboratory tests, all medical imaging, endoscopies, referrals to (other) medical specialist care, referrals to paramedical care, and drug prescriptions. Note that health-care use in both primary and secondary care will be evaluated for patients allocated to any group of randomisation to create a complete survey of health-care use.

Each single item will be stored in the case record file created for each participant. Via this information from health-care use, the costs used by each participant will be determined by using standardised reference lists.

### Ethics and safety

The medical ethics committee of the Academic Medical Centre (Amsterdam, The Netherlands) has approved the study protocol (MEC 2014_332). This study will be conducted according to the principles of Good Clinical Practice.

## Discussion

The aims of this study are to examine the quality of care for patients after colon cancer treatment in primary care and to determine the effect of the use of the eHealth application Oncokompas^2.0^ in these patients. To date, the evidence on this subject has been scarce. Nevertheless, future care for the so-called “cancer tsunami” should be organised efficiently and in the best way for patients, in which currently unmet physical and psychosocial needs are better addressed. The I CARE study will provide evidence regarding the question of whether GPs should have a more prominent role in follow-up and aftercare for patients with colon cancer after their initial treatment. The randomised I CARE study not only evaluates quality of life and patients’ satisfaction but also assesses safety and costs during a 5-year follow-up time.

## Trial status

At the time of submission, the study protocol was approved by our medical ethics committee and registered in the Dutch Trial Register. Recruitment of participants started in April 2015.

## Abbreviations

I CARE: Improving Care After colon canceR treatment in the Netherlands. Personalised care to Enhance quality of life
DSMB: Data and safety monitoring board
EMR: Electronic medical record
EORTC: European Organisation for Research and Treatment of Cancer
EQ-5D-5 L: 5-level version of the EuroQol
GP: General practitioner
ICER: Incremental cost-effectiveness ratio
iMTA MCQ: iMTA Medical Consumption Questionnaire
PRO: Participant-reported outcome
SF-HLQ: Short-Form Health and Labour Questionnaire
